#### Participants

Recruitment (ongoing) will aim for 122 Portuguese breast cancer survivors who have completed primary cancer treatment and are currently under aromatase inhibitors therapy and will subsequently be randomized to receive the brief PA counseling (PAC), the structured exercise program (StEx), or to a waiting list control group.

The inclusion criteria for entering this study are: 1) post-menopausal women, below 70 years old; 2) histologically confirmed hormone-receptor-positive breast cancer (stage I, II, III); 3) having initiated AI hormonal therapy following the primary treatment (surgery, radiotherapy, chemotherapy, etc.), at least 1 month before being enrolled; and 4) ECOG-Performance Status 0–1 (being able to perform light-to-moderate physical activities). The exclusion criteria are: 1) evidence of stage IV cancer or synchronous tumors; 2) uncontrolled hypertension, cardiac or pulmonary disease; 3) contraindications to exercise training according to the assistant doctor; 4) inability to provide informed consent; and 5) expected inability to fulfill the proposed program schedule.

Given the study design, sample size estimations were calculated for primary outcomes having one-way factorial analysis of variance with repeated measures as the reference statistical analysis. Based on previous research findings, and considering a 25% dropout, the sample size was estimated in 98 participants to detect a small to moderate effect size (α = 0.05; statistical power = 0.80) using G*Power 3.1. Consensual criteria on sample size needs for mediator/moderator analyses are not consensual and depend on the procedure and number of indicators and pathways in the models; therefore, we increased the estimated number of participants in 25%, obtaining a final estimated sample size of 122 participants.

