**Primary outcomes**				
Physical activity/sedentary behavior (objective and self-reported)	X	X	X	X
Lifestyle physically active choices	X	X	X	X
Quality of Life	X	X	X	X
Healthcare use	-	X ^a^	-	-

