**Secondary outcomes—Psychosocial Measures**				
Perceived intervention climate	-	X	-	-
Exercise motivational regulations	X	X	X	X
Exercise needs satisfaction/frustration in exercise	X	X	X	X
Affective response to exercise	X	X	X	X
Exercise self-efficacy	X	X	X	X
Self-regulation skills	**-**	X	X	X
Subjective Pain	X	X	X	X
Sleep quality	X	X	X	X
Body image	X	X	X	X
Depressive symptoms	X	X	X	X
Psychological well-being	X	X	X	X

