**Process evaluation (intervention groups-only)**				
Participants focus groups	-	X	-	X

^a^Assessment performed 6 months after intervention’s start

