#### Statistical methods

Factorial Anovas with repeated measures, adjusting for potential covariates (e.g., primary treatment, length of AI therapy), will be conducted for primary and secondary outcomes. The analysis will be intent-to-treat to include compliance effects in the overall assessment. Last Observation Carried Forward will be used to impute missing values. A per-protocol analysis will also be conducted without participants who do not attend at least 80% of the sessions. Normality plots and Kolmogorov–Smirnov tests will be used to test normality of outcome variables. If substantial departure from normality is found, square root log transformations will be computed. If normality is still not satisfied, non-parametric tests (e.g., Kruskal–Wallis) will be employed. As the experimental design is factorial, multiple comparison adjustments will not be appropriate.

Mediators of change, i.e., mechanisms by which participants change their lifestyle behaviors and QoL (vs. controls), will be explored using structural equation modeling (AMOS 18.0) and multiple mediation analysis (PROCESS macro v. 3.3 for SPSS). Putative candidates will include motivational (e.g., autonomous motivations) and self‐regulatory (e.g., action planning) variables. Mediation is said to occur when the causal effect of an independent variable (X) on a dependent variable (Y) is partially or fully explained by a mediator (M) [93]. Indirect effects will be tested using Preacher and Hayes’ procedures [94]. Bootstrapping with 5000 samples and 95% CI estimates for indirect effects will be calculated and assumed significant (α = 0.05) if the CI does not encompass zero [95, 96]. The ratio of the indirect effects to the total effects (P_*M*_) will be calculated to express the strength of the mediation effects [95]. Moderators, i.e., baseline characteristics that have an interactive effect with the intervention on the outcome(s), will be assessed to better understand individual differences in intervention effects [97, 98]. Moderation effects on primary outcomes will be conducted at intervention or follow-up’s end.

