A cost-effectiveness analysis will be conducted, from the NHS and societal perspectives, in comparison with the “no intervention” arm. The time horizon of the study will coincide with that of the intervention follow-up, so that no specific modeling tools will be used. Quality-adjusted life years (QALYs) will be estimated using EORTC QLQ-C30 collected during the intervention, mapped to EQ-5D using mapping algorithms from the literature [97]. Intervention costs will be estimated using a bottom-up approach [99]. Attendance to PA counseling and exercise sessions will be registered; exercise physiologists’ time-related costs will be estimated using their gross hourly salaries, and equipment and disposables’ costs through invoices. Healthcare resources will include consultations, drugs, tests and exams, in-patient stays and day care sessions, valued using usual official tariffs. Absenteeism will be assessed using participants’ reports of their number of absence days or percentage of normal working hours worked, valued at patients’ hourly wage. The incremental cost-effectiveness ratio (ICER) will be calculated as the difference in costs divided by the difference in QALYs between intervention and control groups.

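### Carry-forward, the only missing-data rule, cannot fill a missing healthcare-use record or a missing T1 self-regulation score, so intention-to-treat fails for those variables

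*Protocol article*

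**What the plan says.** Statistical methods plans covariate-adjusted repeated-measures ANOVA for primary and secondary outcomes. On the analysis principle and missing data it then states: "The analysis will be intent-to-treat to include compliance effects in the overall assessment. Last Observation Carried Forward will be used to impute missing values". The article gives no other method for missing values.

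Table 2 gives this schedule:

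| Variable | T0 | T1 (4 months) | T2 (10 months) | T3 (16 months) |
|---|---|---|---|---|
| Activity and sedentary behavior; active choices; quality of life | X | X | X | X |
| Healthcare use (listed as primary) | – | X, footnote a | – | – |
| Self-regulation skills | – | X | X | X |

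The footnote attached to "Healthcare use" reads "Assessment performed 6 months after" the intervention began. The Primary outcomes text instead describes resource use as recorded over the study as a whole, and the cost-effectiveness paragraph sets a time horizon equal to the follow-up.

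Other relevant statements:
- Participants: the sample size was calculated "considering a 25% dropout", and the final target is 122.
- Randomization and blinding: women are randomised only after finishing the baseline assessments.
- Statistical methods: self-regulatory variables, with action planning as the example, are candidate mediators.
- Cost-effectiveness: QALYs come from the QLQ-C30 mapped to EQ-5D, and "The incremental cost-effectiveness ratio (ICER) will be calculated as the difference in costs divided by the difference in QALYs between intervention and control groups". This paragraph names neither an analysis set nor a missing-data rule.

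**The concern.** The issue is not whether carried-forward values are plausible. For some variables the rule returns no value at all. A woman who leaves before the single healthcare-use assessment has nothing to carry, so she drops out of the analysis of an outcome the plan calls primary, although the plan says the analysis is by intention to treat. The same happens to a woman with no T1 self-regulation score, in any comparison or mediation model that uses that score.

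The loss may well be informative. The adherence section calls poor compliance with interventions and assessments a major risk and links expected functional decline to dropout. Health-related dropout is plausibly related to healthcare use, so restricting the outcome to women with a record risks bias as well as lost precision.

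The economic analysis is exposed too. The same woman does have a T0 QLQ-C30, so her quality of life can be carried to every later visit while her healthcare cost stays blank.

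**Working it through.** **1. The plan's own figure.** 98 × 1.25 = 122.5, given as 122. The 98 cannot be rebuilt from the article alone, because no numerical effect size is stated. Assume a group-by-time test with 3 groups, 4 measurements, f = 0.15, correlation 0.5 and no sphericity correction. This gives 78 women (power 0.801), and 78 × 1.25 = 97.5, or 98. A within-factor test with 3 measurements comes close (75 / 0.75 = 100), so the route is inferred. Only 122 and 25% are used below.

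**2. What carry-forward can fill, by variable.**
- Activity and sedentary behavior, active choices, quality of life: a T0 value exists, so T1, T2 and T3 can all be filled.
- Self-regulation skills: a T1 value can be carried to T2 and T3. A missing T1 value has nothing before it.
- Healthcare use: one assessment and nothing earlier. No missing record can be filled.

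**3. How many women.** Let d be the share with no healthcare-use record. The article does not give d. It gives 25% dropout overall, without timing, so a range is shown.
- Missing = 122 × d.
- Standard-error factor against complete data = √(122 / observed).

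**4. The ICER, if utilities are carried forward and healthcare costs are not.** Let ΔC and ΔQ be the healthcare-cost and QALY differences in women with records. Assume d is equal across arms and lost women carry their baseline utility, with no gain. The QALY difference in all randomised women is then (1 − d) × ΔQ, while the cost difference is still ΔC. The healthcare-cost part becomes ΔC / [(1 − d) × ΔQ], which is 1/(1 − d) times its value when both parts use the same women.

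| d | Missing | Observed | SE factor | ICER factor, 1/(1 − d) |
|---|---|---|---|---|
| 5% | 6 | 116 | 1.026 | 1.05 |
| 10% | 12 | 110 | 1.053 | 1.11 |
| 15% | 18 | 104 | 1.083 | 1.18 |
| 20% | 24 | 98 | 1.116 | 1.25 |
| 25% | 30 | 92 | 1.152 | 1.33 |

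**5. Precision at the upper end.** Assume 1:1:1 allocation, which the article does not state. The pairwise difference detectable with 80% power at two-sided 0.05 is (1.960 + 0.842) × √(2/n) in SD units. With n = 122/3 = 40.7 per arm this is 0.62. With n = 92/3 = 30.7 it is 0.72.

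**The case against.** Four objections deserve an answer.

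**Scope.** A reader might infer that the whole intention-to-treat analysis collapses to completers. The documents do not support that. The activity, active-choice and quality-of-life outcomes have a baseline to carry, and self-regulation is affected only where T1 is missing. This objection stands in full.

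**The ICER.** A reader might also infer that the ratio will certainly mix two sets of women. The cost-effectiveness paragraph does not say that utilities are carried forward or who enters the analysis. An analyst could use the same women in both parts, and an article may leave that detail to a fuller plan. The mismatch is therefore conditional. However, restricting both parts to women with cost records would itself abandon the randomised set.

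**Timing.** The single 6-month assessment is one reading of a document that elsewhere describes collection over the study. If use is in fact recorded repeatedly, the gap narrows to women with no record at all, since Table 2 shows no T0 collection. The conflict must be settled first, but settling it does not make carry-forward workable for those women.

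**Size.** The 25% covers the whole study, so putting all of it before month 6 is an upper bound. Month 6 is not one of the four visits, so missing a visit need not mean missing this record. Women lost between T1 and month 6 would carry a T1 utility, not the baseline one. Intervention costs come from attendance, salaries and invoices and do not depend on this assessment. All of this stands, so the factors are illustrative.

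It may also be tempting to add that women with missing baseline covariates would be dropped. Nothing shows this: baseline is completed before randomisation, and the medical reports that women bring are described as confirming their history.

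**Conclusion.** The point holds in a limited form. The only stated missing-data rule cannot work for healthcare use, a named primary outcome, or for self-regulation skills missing at T1. For these variables the analysis would include only women who supplied the record, which contradicts the intention-to-treat statement. This is more than detail left to an analysis plan, because the rule the article fixes fails for an outcome the article names.

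On an assumed 10% to 25% without a healthcare-use record, 12 to 30 of 122 women are affected. At 25% the standard error is about 15% larger than with complete data. The factor of 1.11 to 1.33 applies to the healthcare-cost part of the ICER only. It requires carried-forward utilities, observed-only costs, equal loss across arms and no utility gain in lost women. The article does not exclude that combination, but does not state it either.

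The change should be made. The activity and quality-of-life outcomes are not threatened on this ground.

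**What to change.** **Statistical methods, missing values.** For healthcare use and its cost, and for T1 self-regulation scores, replace carry-forward with multiple imputation using arm, cohort, baseline covariates and the available activity and quality-of-life values. Other methods that need no earlier value would also serve. The essential step is to name one that works for these variables.

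**Cost-effectiveness paragraph.** State that costs and QALYs are analysed in the same randomised women, with costs and utilities imputed jointly.

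**Timing of healthcare use.** Reconcile the T1 column and 6-month footnote of Table 2 with the Primary outcomes text and with the full follow-up horizon, so that the period covered by costs is clear and can be matched to the QALY period.

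**Cost.** Plan wording and some extra programming. Intervals for healthcare use and cost may be slightly wider. The imputation change needs no new data.

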### Objectives

This paper describes the protocol of a pragmatic randomized controlled trial (RCT), PAC-WOMAN, targeting Portuguese post-menopausal women diagnosed with hormone-receptor-positive breast cancer, currently on Aromatase Inhibitors. This project primary aims are:a) To develop and test the long-term (16-month) effectiveness and cost-effectiveness of two 4-month group-based interventions, compared to a control waiting list, on promoting sustained changes in PA, sedentary behavior, QoL, and healthcare services’ use (primary outcomes)b) To compare the effects of both interventions (i.e., brief PA counseling vs. structured exercise) on long-term changes in our primary outcomes, as well as their cost-effectivenessc) Evaluate pretreatment moderators of 4-month and 16-month changes in PA, sedentary behavior, and QoLd) Identify critical motivational (theoretical) mechanisms of change in PA, sedentary behavior, and QoL, and explore their mediating role.

As secondary aims, we will study the impact of both interventions on AI therapy continuation, adverse events of treatment, disease-free survival, body composition, sleep quality, physical parameters (e.g., muscular strength), and psychosocial factors (e.g., body image). Furthermore, process evaluation will also be conducted seeking to analyze implementation facilitators and barriers.

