#### Strategies to improve adherence to interventions and follow-up assessments

One of the major risks in this study is the low compliance of patients to the interventions and assessments. Although most cancer survivors manifest interest in participating in physical activity [15], their lifestyle and implemented routines may interfere with their participation. In addition, a severe decline in physical function is expected to occur during AI therapy, which could potentially lead to increased dropout rates. Nonetheless, the research team includes medical oncologists, physiatrists, and qualified exercise professionals that will assure a close proximity with participants throughout the course of the intervention, assess their experiences and opinions about the program and ways of improving it, and provide a rationale for all the activities involved in the intervention, making sure they continue committed to the trial’s protocol. Moreover, a qualitative analysis (through focus groups) will be applied to enhance the understanding of the patients’ perspectives about: the impacts of the intervention in their daily life; benefits and disadvantages of participation; functional aspects (e.g., dose, procedures, structure) of the intervention; and suggestions of improvement. To increase adherence to follow-up assessments, a session on healthy nutrition for cancer survivors will be offered at this point, as this is a topic that gets a lot of interest among women. Also, at each assessment timepoint, a treat will be offered to participants to stimulate their adherence to the evaluations (e.g., using the gym pool for the day of assessments; a week voucher to try out different gyms), scheduled at a time of their convenience. Participants will also receive an early reminder of the approaching assessment point, and then gentle reminders confirming the date, time, and location of their upcoming visit on the day before.

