### Trial status

Recruitment began in January 2022. Due to the COVID-19 pandemic, recruitment rates were very low. On April 27, 2023, 78 women had been screened by our research team, 68 had accepted to participate and had been randomized. Recruitment is still ongoing and the approximate date to be completed is December 2023. The trial final follow-up is expected to occur in February 2025. The trial is expected to be completed in August 2025.

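### Last Observation Carried Forward is the only missing-data rule stated for a trial about maintenance to 16 months, and it can bias the 16-month contrast in either direction

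*Protocol article*

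**What the plan says.** All references are to the protocol article.

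- **Statistical methods, model:** "Factorial Anovas with repeated measures, adjusting for potential covariates", for primary and secondary outcomes.
- **Statistical methods, population:** "The analysis will be intent-to-treat to include compliance effects in the overall assessment".
- **Statistical methods, missing data:** "Last Observation Carried Forward will be used to impute missing values". No second missing-data approach is named.
- **Statistical methods, second analysis:** "A per-protocol analysis will also be conducted without participants who do not attend at least 80% of the sessions". This set is defined by attendance, so it does not test the carry-forward assumption.
- **Objectives:** the first primary aim is to "test the long-term (16-month) effectiveness and cost-effectiveness of two 4-month group-based interventions" on sustained change in physical activity, sedentary behavior, quality of life and healthcare use.
- **Rationale for the PAC-WOMAN trial:** whether habits last once a programme ends is treated as uncertain and still to be determined.
- **Participants:** the sample size allows for 25% dropout.
- **Assessments:** baseline, 4, 10 and 16 months (T0 to T3).

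**The concern.** Carrying the last value forward supplies part of the answer to the question being asked. Someone who leaves after the month-4 visit is entered at month 16 with the month-4 result, so any gain is recorded as kept. Someone who leaves during the intervention is entered with the baseline value, so any effect is recorded as absent. The 16-month contrast becomes a mixture of real 16-month data, earlier results and baseline values, weighted by when people left.

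At stake is the primary question at its primary time point. A real month-4 effect that has faded could appear partly sustained, and a sustained effect could be diluted. The filled values also enter the analysis as if measured, so the reported precision is close to that of a trial with no missing data.

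**Working it through.** **Inputs from the article.** Visits at 0, 4, 10 and 16 months; 25% dropout; α = 0.05; final sample size 122. The second sample-size step reproduces: 98 × 1.25 = 122.5, reported as 122. Three equal arms would hold about 122/3 ≈ 41 each; equal allocation is assumed because no ratio is given.

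**Assumed, because the article gives no figure.** Outcome SD 1; correlation 0.5 between any two visits; a 0.5 SD gain at month 4; the later course of the effect; the timing of dropout, taken as completely at random and equal across arms.

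**Formula.** Let p be the proportion missing at month 16; d1, d2, d3 the true arm differences at months 4, 10 and 16; and w0, w1, w2 the shares of dropouts last seen at baseline, month 4 and month 10. The baseline difference is 0 by randomization, so w0 contributes nothing:

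E(LOCF contrast) = (1 − p)·d3 + p·(w1·d1 + w2·d2)

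**Results with p = 0.25**

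| Scenario | Calculation | LOCF | True |
|---|---|---|---|
| Gain fully lost (0.5, 0.25, 0), all last seen at month 4 | 0.75×0 + 0.25×0.5 | 0.125 | 0 |
| Same, last visit split equally between months 4 and 10 | 0.75×0 + 0.25×(0.5×0.5 + 0.5×0.25) | 0.094 | 0 |
| Half the gain lost (0.5, 0.375, 0.25), split as above | 0.75×0.25 + 0.25×(0.5×0.5 + 0.5×0.375) | 0.297 | 0.25 |
| Gain sustained at 0.5, all last seen at month 4 or 10 | 0.75×0.5 + 0.25×0.5 | 0.50 | 0.50 |
| Gain sustained at 0.5, all dropouts last seen at baseline | 0.75×0.5 + 0.25×0 | 0.375 | 0.50 |

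Varying only the dropout rate in the first row, 15% gives 0.15 × 0.5 = 0.075 and 35% gives 0.35 × 0.5 = 0.175.

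**Standard error of a two-arm, baseline-adjusted contrast at month 16.** The residual variance is 1 − 0.5² = 0.75.

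- Complete data: √(2 × 0.75/41) = 0.19.
- Available data, with 0.75 × 41 observed per arm: √(2 × 0.75/(41 × 0.75)) = 0.22.
- LOCF in simulation, losses after month 4: about 0.19, or roughly 13% below the available-data value.

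**Simulation** (4,000 runs, 41 per arm, baseline-adjusted comparison at month 16). With the gain fully lost:

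- LOCF rejects the true null in 7.4% of runs (last visit split) to 9.7% (all at month 4).
- Available data reject in 5.1%, with a mean estimate of 0.00.

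A normal approximation agrees: shifts of 0.094/0.19 ≈ 0.49 and 0.125/0.19 ≈ 0.66 standard errors give about 8% and 10%. When there is no effect at any visit, the arm-by-time F test after LOCF rejects in about 5% of runs.

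**The case against.** **Direction and size are not known.** This stands. LOCF assumes kept gains only for losses after month 4. The article gives no dropout timing, and losses during the intervention are at least as plausible. A reader might infer that LOCF always inflates the long-term effect; the last row of the table shows the opposite. With flat paths after dropout the bias is zero. The shifts shown are also at most about half to 0.6 of the available-data standard error (0.125/0.22 ≈ 0.57).

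**Standard errors are not simply wrong.** This largely stands. A reader might infer that the tests are invalid. In simulation the model standard error matched the actual spread of the LOCF estimator, and the flat-null error rate held near 5%. The fair statement is near-complete-data precision around an estimate that may be shifted.

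**The expected decline does not settle the matter.** The section on adherence strategies says "a severe decline in physical function is expected to occur during AI therapy, which could potentially lead to increased dropout rates". It is tempting to read this as a forecast that LOCF will create an arm difference. But physical function is a secondary outcome, all arms receive the therapy, and a common decline distorts an arm contrast only if dropout differs by arm in amount or timing. The article forecasts no such difference.

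**The alternative is not immune.** This stands too. The simulated dropout was completely at random, so available data were unbiased by construction. If leaving depends on unobserved values, a mixed model is also biased.

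**Further analyses may sit in an analysis plan not shown.** True, so no weight is placed on absent sensitivity analyses. The choice of LOCF is stated outright, and that is what is criticized.

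**Dates.** The Trial status section gives recruitment to about December 2023 and says "The trial final follow-up is expected to occur in February 2025". December 2023 plus 16 months is April 2025. A reader might infer that late enrolees will miss T3 and be filled from month 10. The dates are approximate and nothing says this, so it is not part of the point.

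**Conclusion.** The point holds in this form: LOCF is poorly suited as the stated primary missing-data rule when the primary question is maintenance to 16 months and a quarter of participants are expected to drop out. It can bias the 16-month contrast upward or downward according to when people leave and whether effects fade.

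Under the assumptions above, the error runs from about +0.09 to +0.125 SD when a 0.5 SD gain is fully lost and losses follow month 4, to about −0.125 SD when the gain is sustained and all losses precede month 4. The first case carries a false-positive rate of about 7 to 10%. These figures rest on assumed decay, timing, SD and correlation, and illustrate the possible size without predicting it. What does not depend on them is that the rule fills in an answer to the maintenance question for everyone not seen at month 16.

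**What to change.** Replace the repeated-measures ANOVA with LOCF by a likelihood-based linear mixed model for repeated measures:

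- all observed T1 to T3 values, without imputation;
- arm, visit and arm-by-visit terms, with unstructured covariance;
- the baseline value of the outcome as a covariate;
- the 16-month arm contrasts named as the primary estimates.

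Add one sensitivity analysis by multiple imputation, control-based or delta-adjusted, because the mixed model is itself biased if dropout depends on unobserved values. Include in it participants with no post-baseline value, who contribute nothing to a model of T1 to T3.

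**Cost.** Analysis wording, a little more analysis work and slightly wider intervals (a standard error of about 0.22 instead of 0.19 under the assumptions above). No new data are needed. The Randomization and blinding section says outcome data stay blinded until data entry is complete, so the change can be fixed before unblinding.

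As a separate item, reconcile the recruitment end, the 16-month visit and the final follow-up date in Trial status.
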